#### HIV Testing

All participants without a recent (i.e., within the prior three months) HIV test result reported in the DIC registry will also undergo rapid HIV testing conducted by study staff trained and certified in HIV counselling following NASCOP/Government of Kenya standards [57, 58]. Due to changes in Kenya’s testing guidelines [59], testing used Abbott Determine HIV-1/2 and Abbott First Response HIV-1/2 RDT kit for those with a reactive Determine test May 2022 to February 2025, and Trinscreen from March 2025 onward. Once results are ready, staff will inform participants of their results and conduct post-test counselling. The participants will be referred to the NSP site for appropriate HIV care referral.

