#### Positive Cohort Follow-Up

Participants who test HIV- or HCV antibody-positive at baseline or had a recent positive test recorded will undergo three follow-up visits at four-month intervals in the year following their baseline visit. Participants are given a one-month grace period before and after the four-month mark in which they can complete the visit. Participants who miss a visit are still eligible to complete later follow-up visits. Peer case managers at each site will assist study staff with recalling participants for their follow-up visits by conducting outreach at commonly frequented injection venues. At each of the three follow-up visits participants will complete biobehavioral and social network surveys with updated time frames, and will receive HIV, HCV, and HBV testing.

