#### Negative Cohort Follow-Up

Due to resource limitations, it will not be possible to conduct multiple follow-ups for all participants. Following completion of the positive cohort follow-up visits, we will conduct one additional follow-up visit for individuals who test HIV- and HCV antibody-negative during their baseline visit to determine seroconversion with HIV, HCV, and/or HBV. Biobehavioral and social network data will also be collected during these follow-ups.

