### Additional Planned Analyses

Baseline and follow-up demographic and clinical information will be used to assess demographic, behavioral, structural, virologic, and geographic risk factors associated with positions of high centrality; additionally, we will assess associations between centrality measures and HIV, HCV, and HBV disease status. To assess centrality, we will create a unified network using egocentric social network data, RDS data, and token data; and use results from the GHOST analysis to examine how transmission occurred within these other networks. Tabular analysis will be used to explore bivariate associations between these characteristics, risk behaviors, and the presence of HIV/HCV co-infection or multiple-strain HCV infection. Factors strongly associated with having high centrality with *p*-values less than 0.2 will be considered for inclusion in multivariable models. Because RDS sample is not a random sample, we will conduct weighted regression analyses by using RDS weights, which are calculated as inverse of self-reported network size [64].

To evaluate the effect of having high centrality on transmission and acquisition of blood borne infections, cox proportional hazard models (adjusting for host demographic, risk behavior and clinical factors) will be used to estimate the hazard ratios for associations between HIV/HCV co-infection, multiple-strain infection, and other factors associated with having high centrality on the probability of incident blood borne infections. Incidence rates per 100 person-years of HIV and HCV were estimated to be 2.5 and 6.3 in the coastal region, 1.6 and 2.3 in Nairobi, and less than 1 in the Western region, based on previous data [12].

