## Limitations

The assertion that individuals who are highly central will be at high risk of receiving and transmitting HIV, HCV and other BBIs may not be evident in this population of PWID. Moreover, the association of HIV/HCV co-infection, multiple-strain HCV infection, or other factors may not be able to be demonstrated in this sample due to sample size constraints. Additionally, though we believe RDS to be the best sampling method for this work, it may also introduce some bias to the study. For example, though RDS assumes recruiters will pass their coupons and tokens to network contacts, it is possible that they may pass the coupon off to a stranger (e.g., someone visiting the NSP site at the same time). Coupon distribution behaviors (e.g., who is approached, why and how they are approached, who accepts and why they accept) may also vary between individuals, leading to undocumented variation. In highly clustered populations, it is also possible that the RDS sample will not mix well and draw from the full target population with the expected proportions. This could lead to undue influence of the seeds on the final sample. This method of recruitment by referral also naturally biases selection towards individuals with a larger number of contacts. Individuals with no contacts will not be represented in the sample. Additionally, given that each referral chain starts at a single location, the geographical distribution cannot be expected to be representative of the whole population of PWID. PWID living close to a seed location are more likely to be included. Additionally, those living far away from an NSP site may be less likely to return a coupon.

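### The Cox models are credited with estimating the effect of centrality on transmission, but their outcome is the participant's own new infection, so they address acquisition only

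*Protocol article*

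**What the plan says.** All references are to the protocol article.

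- **Aim.** Additional Planned Analyses opens the relevant paragraph with "To evaluate the effect of having high centrality on transmission and acquisition of blood borne infections, cox proportional hazard models". Two targets are named: passing infection on, and receiving it.
- **Outcome.** The same sentence says the hazard ratios are for "associations between HIV/HCV co-infection, multiple-strain infection, and other factors associated with having high centrality", and that the effect is "on the probability of incident blood borne infections". No second outcome is given.
- **How the outcome is observed.** Negative Cohort Follow-Up has one later visit "to determine seroconversion with HIV, HCV, and/or HBV". Positive Cohort Follow-Up has three visits, at which participants "will receive HIV, HCV, and HBV testing". Both record the tested person's own status.
- **Laboratory work.** HCV Testing, HCV Sequencing and Analysis, and Phylogenetic network describe sequencing of HCV. For HIV, participants "will also undergo rapid HIV testing conducted by study staff"; for HBV a rapid surface-antigen test is described. The article describes no sequencing of either.
- **Transmission elsewhere.** Additional Planned Analyses also plans to lay the GHOST results over a unified network built from coupons, tokens and egocentric reports, to study factors linked to the direction of HCV transmission, and to build an agent-based model of HIV and HCV.

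**The concern.** The aim and the outcome of one analysis do not match. A model of the time to a participant's own new infection says who becomes infected. It does not record whom that participant infected.

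This matters because the study's central assertion has both halves: Limitations describes it as the claim that "individuals who are highly central will be at high risk of receiving and transmitting HIV, HCV and other BBIs". If the Cox result is reported under its stated aim, a hazard ratio above 1 would be presented as an effect on transmission, and a null result as the absence of one. Neither follows from the model. The transmission half is also the one most directly relevant to directing treatment and prevention at central people.

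**Working it through.** The article gives no event count, power or effect size for the Cox models, so there is no planned figure to reproduce. The check has two steps.

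**1. Aim against outcome.**

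| Element | What is specified | What it informs |
|---|---|---|
| Stated target | Transmission and acquisition, all blood borne infections | Both |
| Outcome | Incident infection in the participant | Acquisition |
| Observation, negative cohort | Own seroconversion at one visit | Acquisition |
| Observation, positive cohort | Own retests at three visits | Acquisition |
| HCV sequence links (separate analysis) | Pairs, clusters, direction | Transmission, HCV only |

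For a first infection with a given virus, the people already infected are the possible sources. They are outside the risk set for that event, so their onward transmission does not enter its hazard ratio.

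**2. When do the two quantities agree?** None of these inputs is in the article; all are assumptions. Central people make up 20% of 2,500, and 20% of each group are infected. The hazard is β = 0.06 per infected contact, mixing is random and ties are complete. Let d_c and d_n be the number of ties of central and other people. Let t be the infectivity per tie of central people relative to others, and s their relative susceptibility. Under random mixing both groups face contacts of the same average infectivity, so to first order:

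- own-infection ratio = (d_c / d_n) × s
- onward-transmission ratio per infected person = (d_c / d_n) × t
- ratio by centrality of a single infected contact = t

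The first two are equal only when s = t. Simulations with 300 replicates per scenario gave:

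| Scenario | Own-infection: formula, simulated | Onward: formula, simulated | Per-contact: formula, simulated |
|---|---|---|---|
| 4 v 4 ties, t = 3, s = 1 | 1, 0.99 | 3, not tabulated | 3, 3.04 |
| 4 v 4 ties, t = 1, s = 2 | 2, 1.97 | 1, not tabulated | 1, 0.95 |
| 8 v 4 mutual ties, t = s = 1 | 2, 1.97 | 2, 1.99 | 1, 1.00 |
| 12 v 4 mutual ties, t = s = 1 | 3, 2.90 | 3, 3.02 | 1, 1.01 |

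In the first two rows, acquisition and transmission come apart completely. In the last two they move together. An observed own-infection ratio near 2 fits both the second row (no extra transmission) and the third (twice as much). The Cox model cannot separate them.

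The last column shows a second point. A model of infection on the centrality of a person's infected contacts, adjusted for their number, estimates infectivity per tie. It returns about 1 when central people cause two to three times as many infections simply by having more ties.

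**The case against.** The strongest reply is that transmission is not neglected. HCV sequence links are to be examined within the same network from which centrality is computed, direction of HCV transmission is to be studied, and the effect of targeting is to be predicted by the agent-based model, not read from a hazard ratio. Limitations also warns that the central assertion may not be borne out. All of this stands. A reader might infer that the study has no means of studying transmission; for HCV the documents say otherwise.

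Second, a reader might infer that a transmission effect would be invisible to the Cox model. That is too strong. The article's Introduction describes high centrality as being highly connected, and Recruitment network names degree among its measures. If centrality acts only through the number of mutual ties, own infection and onward transmission rise together, as the last two rows of the table show. This stands as a limit on the point, but it does not make acquisition a general measure of transmission.

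Third, a reader might infer that infected participants contribute nothing to the models. That holds only for first infection with the virus they already carry. The positive cohort is retested for all three viruses, so a person with HIV remains at risk of HCV or HBV. That event is still the person's own acquisition.

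Fourth, the absence of HIV and HBV sequencing might be taken as an error. It is a design choice, and the Introduction explains why HCV diversity is used to study these networks. It matters here only because it limits what can be concluded about onward transmission of those two viruses.

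**Conclusion.** The point holds as a misattribution. The sentence claims two targets and the model reaches one. This follows from the article's own wording and rests on no numerical assumption.

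The size of the resulting error cannot be fixed from the documents. In the illustrative settings it ranges from almost none (1.97 against 1.99) to a threefold difference missed altogether (0.99 where the true infectivity ratio is 3). These figures assume random mixing, complete ties and equal prevalence of infection in both groups. They show the logic and do not predict study results.

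For HCV, other planned analyses must answer the transmission question. For HIV, the article describes only the agent-based model, which is calibrated to surveys and disease status and does not observe who infected whom. For HBV, it describes no transmission analysis that rests on observed links, and the agent-based model does not cover it.

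**What to change.** In Additional Planned Analyses:

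1. Limit the aim of the Cox models, and any conclusion drawn from them, to acquisition of infection.
2. Assign the transmission question to the HCV analyses already planned, by relating GHOST-defined links and direction to the centrality of the linked participants in the unified coupon, token and egocentric network.
3. State that no transmission links are observed for HIV or HBV, so no empirical conclusion about onward transmission by central people will be drawn for these viruses; for HIV, the agent-based model is the only source.
4. If a model based on contacts' centrality is added, make it secondary and describe it as estimating infectivity per tie, not total onward transmission.

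No new data are needed. The cost is a change of wording and an explicit link between two analyses already planned. The drawback is a transmission conclusion that is confined to HCV and less precise, because it rests on sequenced participants.

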Despite the successful implementation of these programs, challenges remain [22]. A recent global systematic review found that Kenya had fairly low NSP and OAT coverage relative to the number of PWID in the country [23] and funding gaps for these harm reduction programs pose obstacles to consistency of care provision and opportunities to expand services [24]. Additionally, challenges with availability and access to commodities for testing and treatment, and financial and policy barriers pose obstacles to greater DAA scale-up and uptake [10]. Recent funding cuts to global health organizations have also drastically impacted clinics and drop-in centers offering HIV and HCV care, substance use disorder treatment, and harm reduction services [25–27].

Social network characteristics play an important role in HIV and HCV transmission among PWID [28–32]. Factors like network size, composition and characteristics, and density have been shown to be associated with multiple behaviors associated with both HIV and HCV risk, including sharing of needles/syringes and other injection paraphernalia [33]. Individuals’ positions within a social network can also be ranked using different measures of centrality such as degree, closeness, betweenness, and Eigenvector centrality. Highly central positions (i.e., being highly-connected at the center of a network) have been linked with HIV and HCV infection, as well as risky injection and sexual behaviors [31, 34, 35]. Little network simulation research has been conducted in Sub-Saharan Africa, and it is unclear how generalizable findings from other settings may be to Sub-Saharan Africa, warranting further investigation in the region.

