## Methods

### Study Objectives

The primary aim of the study is to characterize PWID networks, including HCV transmission networks, and identify high centrality PWID. We also aim to determine demographic, behavioral, virologic, and geographic risk factors associated with highly central PWID. We hypothesize having a highly central position will be associated with the greatest risk of HIV and HCV. Furthermore, we will develop mathematical models to examine population-level effects of targeted, network-based interventions to reduce transmission of HIV, HCV, and other BBIs.

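### The Cox model meant to evaluate high centrality names only correlates of centrality as exposures, and two of these cannot be exposures for some first infections

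*Protocol article*

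**What the plan says.** The purpose of the Cox models is given in the protocol article under Additional Planned Analyses: "To evaluate the effect of having high centrality on transmission and acquisition of blood borne infections". The same sentence says that they will estimate hazard ratios for "associations between HIV/HCV co-infection, multiple-strain infection, and other factors associated with having high centrality on the probability of incident blood borne infections", "adjusting for host demographic, risk behavior and clinical factors".

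The hypothesis under Study Objectives has network position as the exposure: "We hypothesize having a highly central position will be associated with the greatest risk of HIV and HCV".

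Three other statements bear on who can have an incident event:

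- Negative Cohort Follow-Up plans one later visit for "individuals who test HIV- and HCV antibody-negative during their baseline visit to determine seroconversion with HIV, HCV, and/or HBV".
- Positive Cohort Follow-Up takes anyone positive for HIV or for HCV antibody, so it includes people with only one of the two infections. They are retested for HIV, HCV and HBV at three visits.
- HCV Testing restricts sequencing to participants with detectable HCV RNA. Multiple-strain status is therefore known only for people who already have HCV.

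Earlier in Additional Planned Analyses there is a separate, general plan: "we will assess associations between centrality measures and HIV, HCV, and HBV disease status".

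**The concern.** The sentence sets one question and names the terms of another. A hazard ratio for co-infection, or for any other marker that goes with centrality, is not the effect of centrality. Without a centrality term the model gives no estimate of that effect.

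The named exposures also sit badly with the outcome. Co-infection and multiple-strain HCV are themselves defined by infections that the model counts as incident events. Someone who already has the infection cannot acquire it for the first time.

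At stake is the only time-to-event analysis in the article, and so the only one specified to put network position before infection. If it is run as written, the hypothesis on incident infection goes untested. Some of the reported hazard ratios would be either unavailable or, under a pooled endpoint, a product of who is susceptible.

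**Working it through.** The article gives no power, event count or target hazard ratio for this model, so there is no figure to reproduce. The check rests on logic, with two illustrations.

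**Step 1: aim against terms.**

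| Element | What the article gives |
|---|---|
| Aim | effect of high centrality |
| Exposures | co-infection, multiple-strain infection, other correlates of centrality |
| Adjustment | demographic, risk-behaviour and clinical factors |
| Outcome | incident blood-borne infection |

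Centrality appears in the aim row only.

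**Step 2: risk sets by baseline status.**

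| HIV | HCV | At risk of first HIV | At risk of first HCV |
|---|---|---|---|
| negative | negative | yes | yes |
| negative | single strain | yes | no |
| negative | multiple strains | yes | no |
| positive | negative | no | yes |
| positive | single strain | no | no |
| positive | multiple strains | no | no |

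- Co-infection (last two rows) has no person-time in either risk set.
- Multiple-strain HCV (third and sixth rows) has none for first HCV. The third row remains at risk of first HIV and is retested for it in the positive cohort.
- In the negative cohort both exposures are absent for everyone at baseline.
- Time-updating does not help. A person becomes co-infected only once both first infections have occurred, and multiple-strain HCV cannot precede first HCV.
- Any of these groups can still have incident HBV if HBsAg-negative, or an HCV reinfection if that is counted.

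Three hazard ratios are therefore not estimable: co-infection for first HIV, co-infection for first HCV, and multiple-strain HCV for first HCV.

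**Step 3: what pooling could do (illustration).** The article does not say that infections are pooled. Suppose they were. The coastal rates in Additional Planned Analyses are 2.5 (HIV) and 6.3 (HCV) per 100 person-years. No HBV rate is given, so h = 0.5 to 2 is assumed. With no true effect of co-infection:

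- Reinfection not counted, comparator susceptible to all three viruses: HR = h/(2.5 + 6.3 + h). For h = 0.5 this is 0.5/9.3 = 0.05; for h = 1, 1/9.8 = 0.10; for h = 2, 2/10.8 = 0.19. In Nairobi (1.6 and 2.3) with h = 1: 1/4.9 = 0.20.
- Same coastal setting, h = 1, comparator HCV-positive only: 1/(2.5 + 1) = 0.29.
- Same coastal setting, h = 1, fully susceptible comparator, reinfection counted at an assumed 6.3: (6.3 + 1)/9.8 = 0.74.

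The direction is the same in each case, towards apparent protection. The size moves from 0.05 to 0.74 with assumptions that the article does not settle.

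**Step 4: whether the corrected model has events (illustration).** Assume one person-year each, no dropout, 3500 enrolled, 11.2% HIV prevalence (the Sub-Saharan figure in the Introduction), HCV prevalence of 22%, 13% and 1% on the coast, in Nairobi and in the West, and Western incidence of 0 to 1 per 100 person-years.

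- Equal split (1166.7 per region), Western incidence 0: first HIV 1166.7 × (0.025 + 0.016) × 0.888 = 42.5; first HCV 1166.7 × (0.78 × 0.063 + 0.87 × 0.023) = 80.7.
- Split by number of sites (1647, 1029, 824), Western incidence 1: first HIV (41.2 + 16.5 + 8.2) × 0.888 = 58.5; first HCV 80.9 + 20.6 + 8.2 = 109.7.

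A centrality hazard ratio is therefore estimable for each virus, though not precisely. By Schoenfeld's formula, 80% power for a hazard ratio of 2 (two-sided 5%) needs 103 events if 20% of participants are highly central, and 182 if 10% are.

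**The case against.** The best defence is that this is one sentence in a condensed article. Its opening words show that centrality was in mind, and a full analysis plan may define exposures, events and risk sets. That is fair as to missing detail. It does not answer the point, because the article does list the exposures and the adjustment terms, and centrality is in neither list.

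Other objections limit what can be concluded:

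- A reader might infer that nobody with co-infection or multiple-strain HCV can have an event. The documents do not support this. HIV-negative people with multiple-strain HCV are at risk of first HIV and are retested. The outcome is also wider than first HIV and first HCV: HBV is included, and HCV reinfection is not excluded.
- A reader might infer that the plan contains a hazard ratio biased to 0.05–0.20. It does not. Those values need a pooled endpoint, no reinfection events, an assumed HBV rate and a fully susceptible comparator, none of which the article states.
- A reader might infer that centrality is never related to infection. It is, through the planned association with disease status. But no time-to-event analysis is specified there, and association with existing infection cannot separate acquisition risk from infection that shaped the network.
- A reader might infer that transmission is not addressed at all. Additional Planned Analyses also covers the direction of GHOST-defined transmission events and an agent-based model.
- A reader might infer that adjusting for risk behaviour removes the effect of centrality. The Introduction says only that features such as network size, composition and density are "associated with multiple behaviors associated with both HIV and HCV risk, including sharing of needles/syringes". That is association; behaviour may confound as well as mediate.

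The Limitations section concedes that associations with co-infection or multiple-strain infection may not be shown because of sample size. That is a different matter: an exposure absent from the risk set is not rescued by more participants.

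**Conclusion.** The point holds in a limited form. The Cox model as written does not estimate the effect of high centrality that it is introduced to evaluate, and so does not test the hypothesis on incident infection. Three of the implied hazard ratios cannot be estimated for baseline status: co-infection for first HIV, co-infection for first HCV, and multiple-strain HCV for first HCV. This follows from the stated terms and the definitions of the cohorts and needs no numerical assumption.

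Multiple-strain HCV remains a usable exposure for first HIV in HIV-negative people, and either factor remains usable for incident HBV. The possible distortion under pooling is a risk to close off, not an error that the plan has made; its size depends on the HBV rate, reinfection and the comparator. The illustrative event counts do not bear on the conclusion.

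**What to change.** Rewrite the Cox paragraph as follows.

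1. Name the baseline centrality measure as the exposure.
2. Fit one model per infection, each with its own risk set: first HIV in HIV-negative participants, first HCV in HCV antibody-negative participants, and HBV in HBsAg-negative participants. If HCV reinfection is intended, make it a separate endpoint.
3. Draw each risk set from the negative cohort and from those members of the positive cohort who are still at risk, including the mono-infected.
4. Use co-infection and multiple-strain status only where the person remains at risk, for example multiple-strain HCV for incident HIV in HIV-negative people, or either for incident HBV. Otherwise use them as factors in the GHOST-based onward-transmission analyses already planned.
5. Optionally, report the centrality estimate with and without adjustment for risk behaviour.

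The cost is analysis wording; the visits, tests and network data are already planned. The co-infection hazard ratios for first HIV and first HCV and the multiple-strain hazard ratio for first HCV are given up, but the data could not have supplied them.
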